## Abstract

**Background:**

Suicide is the leading cause of death among Australians. One commonly cited explanation is the impact of social media, in particular, the ways in which young people use social media to communicate about their own experiences and their exposure to suicide-related content posted by others. Guidelines designed to assist mainstream media to safely report about suicide are widespread. Until recently, no guidelines existed that targeted social media or young people. In response, we developed the #chatsafe guidelines and a supporting social media campaign, which together make up the #chatsafe intervention. The intervention was tested in a pilot study with positive results. However, the study was limited by the lack of a control group.

**Objective:**

The aim of this study is to assess the impact of the #chatsafe social media intervention on young people’s safety and confidence when communicating on the web about suicide.

**Methods:**

The study employs a pragmatic, parallel, superiority randomized controlled design. It will be conducted in accordance with the Consolidated Standards of Reporting Trials statement over 18 months. Participants will be 400 young people aged 16-25 years (200 per arm). Participants will be recruited via social media advertising and assessed at 3 time points: time 1—baseline; time 2—8-week postintervention commencement; and time 3—4-week postintervention. They will be asked to complete a weekly survey to monitor safety and evaluate each piece of social media content. The intervention comprises an 8-week social media campaign including social media posts shared on public Instagram profiles. The intervention group will receive the #chatsafe suicide prevention content and the control group will receive sexual health content. Both groups will receive 24 pieces of content delivered to their mobile phones via text message. The primary outcome is safety when communicating on the web about suicide, as measured via the purpose-designed #chatsafe online safety questionnaire. Additional outcomes include willingness to intervene against suicide, internet self-efficacy, safety, and acceptability.

**Results:**

The study was funded in November 2020, approved by the University of Melbourne Human Research Ethics Committee on October 7, 2022, and prospectively registered with the Australian New Zealand Clinical Trials registry. Trial recruitment began in November 2022 and study completion is anticipated by June 2024.

**Conclusions:**

This will be the first randomized controlled trial internationally to test the impact of a social media intervention designed to equip young people to communicate safely on the web about suicide. Given the rising rates of youth suicide in Australia and the acceptability of social media among young people, incorporating social media–based interventions into the suicide prevention landscape is an obvious next step. This intervention, if effective, could also be extended internationally, thereby improving web-based safety for young people not just in Australia but globally.

**Trial Registration:**

Australian New Zealand Clinical Trials Registry ACTRN12622001397707; https://anzctr.org.au/Trial/Registration/TrialReview.aspx?id=384318

**International Registered Report Identifier (IRRID):**

DERR1-10.2196/44300

## Introduction

### Background

Suicide is the leading cause of death among Australians younger than 25 years, and rates have been increasing over the past 10 years [1]. The pathways that lead a young person to feel suicidal are complex and diverse; however, 1 commonly cited explanation for the recent rise in rates of youth suicide is the impact of social media [2].

Young Australians spend over 3 hours per day on social media, and this sometimes includes communicating with others about their own experiences of suicide and being exposed to suicide-related content posted by others [2-4]. While there are many potential benefits to communicating on the internet about suicide, such as the ability to seek and provide support from others in an accessible and nonstigmatizing manner [3,5], the potential for harm also exists. For example, there are concerns that certain types of content (eg, graphic information or images) may cause distress, lead to imitative suicidal behavior, and have been thought to contribute to suicide clusters [6]. In addition, young people may be exposed to expressions of suicide risk posted by others but feel ill-equipped to respond [7].

Guidelines designed to assist mainstream media outlets to report on suicide in a sensitive manner are widespread and have led to improved safety and quality of communication about suicide [8]. They also appear to be linked to a reduction in suicide rates [9]. However, until recently, no guidelines existed that targeted either social media or young people, who are now creators of their own content.

In response to this, we developed the #chatsafe guidelines [10], which were the first set of guidelines in the world specifically designed to better equip young people to communicate safely on social media about suicide. They were developed using the Delphi consensus method in partnership with young people, media, and suicide prevention professionals [11]. The guidelines consist of five sections: (1) things to consider before you post about suicide; (2) sharing your own thoughts, feelings, or experience with suicidal behavior; (3) communicating about someone you know who is affected by suicidal thoughts, feelings, or behaviors; (4) responding to someone who may be suicidal; and (5) memorial websites, pages, and closed groups.

The guidelines were supported by a national social media campaign designed to make the content of the guidelines more accessible to young people. The campaign was co-designed with young people from across Australia [12] and was initially rolled out nationally in 2019, reaching around 1.5 million young people. Together, the guidelines and campaign make up the #chatsafe intervention.

### Aims and Hypotheses

The overall aim of the study is to assess the impact of the #chatsafe social media intervention on young people’s safety and confidence when communicating on the internet about suicide. In this study, the treatment group who will receive the #chatsafe social media intervention will be compared to the control group who will receive social media content providing education on sexual health and well-being.

It is hypothesized that (1) At postintervention (T2), the treatment group will have higher mean scores than the control group on their understanding and compliance with the #chatsafe guidelines, as measured by the #chatsafe online safety questionnaire. Specifically, this will be assessed by improvements in their understanding of language to use or not use, support services available to them, how to share their own experiences of suicide safely, how to communicate about those who have died by suicide, and how to support someone that they are worried about. (2) At the postintervention time point (T2), the treatment group will have higher mean scores than the control group on self-reported (i) safety and confidence when communicating on the internet about suicide, (ii) willingness to intervene against suicide on the internet, and (iii) perceived internet self-efficacy. (3) It will be safe and acceptable to share the #chatsafe intervention with young people entirely via social media (assessed weekly throughout the intervention and postintervention [T2]). (4) Knowledge gains made in the intervention group at T2 will be maintained at T3.

Subgroup differences in perceptions toward the intervention and outcomes of the intervention (ie, gender, sexuality, age groups, and level of social media usage) will also be examined.

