## Methods

### Study Design

The study uses a pragmatic, parallel, superiority randomized controlled design, where the intervention condition (the #chatsafe suicide prevention intervention) is compared to a control condition (sexual health content). It will be conducted over an 18-month period with up to a 12-month recruitment period and an 8-week intervention phase.

Participants will be assessed via self-report surveys at 3 time points: time 1 (T1)—baseline; time 2 (T2)—8-week postintervention commencement; and time 3 (T3)—4-week postintervention. In addition, participants will be asked to complete a short weekly survey to monitor safety and allow evaluation of each piece of social media content. All participants will be reimbursed for their time at a rate of Aus $45 (US $31.95) per hour.

The study is being led by researchers based at Orygen and the Centre for Youth Mental Health, University of Melbourne, Melbourne, Victoria, Australia. It will be conducted and reported in accordance with the Consolidated Standards of Reporting Trials statement [14] (Figure 1).

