### Study Outcomes

The primary outcome is safety when communicating online about suicide, as measured via the purpose-designed #chatsafe online safety questionnaire at T2. This measure was specifically designed for this purpose by 3 study authors (JR, [name], and CC).

Secondary outcomes are (1) confidence when communicating on the internet about suicide, as measured via the purpose-designed #chatsafe online safety questionnaire at T2; (2) willingness to intervene against suicide on the internet, as measured via the Willingness to Intervene Questionnaire at T2 [15]; (3) internet self-efficacy, as measured by the Internet Self-Efficacy Questionnaire at T2 [16]; (4) safety of the weekly #chatsafe content, as measured by the purpose-built weekly evaluation and engagement survey; (5) acceptability of the #chatsafe intervention, as measured by the purpose-built T2 evaluation questions; and (6) safety of the #chatsafe social media intervention (as a whole), as measured by the number of (or absence of) adverse events recorded throughout the trial. Participant adverse events include (1) participant response to item 9 on the 9-item Patient Health Questionnaire [17] at baseline (time 1), time 2, or time 3. (2) Participant response to the 9-item weekly evaluation survey indicates distress, measured by participants selecting “very distressed” in response to the question “To what extent did you find the content this week distressing?” (3) Participant response to the T2 evaluation questionnaire indicates that a particular piece of campaign content made them feel distressed or at risk of suicide. (4) The participant directly contacts the research team via social media or email and reports distress or risk of harm to self. All adverse events will be responded to by the study team, in line with the study’s safety management strategy. (7) Feasibility of the #chatsafe social media intervention was measured by campaign reach via social media analytics, and participant retention or attrition via audit of study enrollment and withdrawal logs. (8) Self-reported evaluations of the acceptability of receiving the #chatsafe social media intervention were measured by purpose-designed study questions. Exploratory outcomes are as follows: (1) subgroup differences (gender, age, previous exposure to, previous experiences of suicide and self-harm, and level of social media usage) at T2 and (2) self-reported open-ended evaluations of the safety, feasibility, and acceptability of receiving the PROSPEct social media intervention for sexual health promotion in the control group at T2.

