
### Outcome Measures

Outcome measures together with the assessment schedule are presented in Table 1. Note that all participants complete the same questionnaires (T1, T2, T3, and purpose-designed 3-item weekly evaluation and engagement survey) regardless of the arm they are allocated to.

**Table 1 table1:** Schedule of assessments and measures.

Measure	Baseline (T1, week 1)	Intervention (weeks 2-9)	Postintervention (T2, week 9)	Follow-up (T3, week 13)
Purpose designed #chatsafe online safety questionnaire	✓	N/A^a^	✓	✓
Patterns of Social Media Use Questionnaire (including 12 items to assess social media usage for the purposes of communicating about suicide and-self harm specifically)	✓	N/A	✓	✓
Perceived Internet-Self Efficacy Scale	✓	N/A	✓	✓
Willingness to Intervene Against Suicide Questionnaire	✓	N/A	✓	✓
Patient Health Questionnaire-9	✓	N/A	✓	✓
Purpose designed 7-items assessing exposure to, and personal experiences of, suicide and self-harm	✓	N/A	✓	✓
Purpose designed 9-item Weekly Evaluation and Engagement survey	N/A	✓	N/A	N/A
Purpose designed 1-item assessing participant reasons for withdrawal/noncomplete	✓	✓	✓	✓
Purpose designed 10-items assessing participants’ evaluations of the intervention content immediately postintervention	N/A	N/A	✓	N/A
Sexual Health Capacity Scale	✓	N/A	✓	✓
Self-Efficacy Protective Sexual Behaviours Scale	✓	N/A	✓	✓
Sexual Health Questionnaire	✓	N/A	✓	✓

^a^N/A: not applicable.

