### Statistical Analysis

At baseline, state of residence, postcode, age, Aboriginal or Torres Strait Island status, gender identity, sexual orientation, primary language spoken at home, cultural background, and educational and occupational background will be reported using descriptive statistics and will be checked for imbalance between trial arms. The moderating effect of gender (male, female, trans, and gender diverse), age group (ie, 16-20 and 21-25 years), time spent on social media, psychological distress, and previous experience of suicide and self-harm will be considered in analyses as covariates.

Analyses will be performed on an intention-to-treat basis, where all individuals randomized will be included in the analysis by their allocated trial arm status regardless of whether they received all, part, or none of the intended treatments. For the primary analysis, we will use linear regression to estimate the difference in the mean changes between the intervention and control arms at T2 in the outcome safety when communicating online about suicide, as measured via the #chatsafe online safety questionnaire. This analysis will adjust for T1 scores. Multiple imputation will be used to address attrition bias, with 50 imputation samples generated using chained equations. We will conduct 2 sensitivity analyses. One sensitivity analysis will be undertaken using complete cases only (ie, repeating the primary analysis but only analyzing participants who have complete T1 and T2 data). The second sensitivity analysis will use multiple imputation and include the following potential moderating factors as covariates: gender (male, female, transgender, and gender diverse), age group (ie, 16-20 and 21-25 years), time spent on social media, psychological distress, and previous experience of suicide and self-harm.

The secondary outcomes at T2 and T3 will be analyzed based on the primary analysis and the 2 sensitivity analyses. We will use linear regression for continuous outcomes, logistic regression for binary outcomes, and negative binomial regression for counts.

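### Hypothesis 4 is a T2-to-T3 claim inside the intervention arm, but the only T3 analysis stated compares arms on secondary outcomes, and the online safety score is not one of them

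*Protocol article*

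**What the plan says.** - **Hypothesis** (Aims and Hypotheses): "Knowledge gains made in the intervention group at T2 will be maintained at T3". Hypotheses 1 and 2 in the same section are worded as treatment against control at T2. Hypothesis 1 ties understanding of the guidelines to the online safety questionnaire.
- **Primary outcome** (Study Outcomes): online communication safety, "as measured via the purpose-designed #chatsafe online safety questionnaire at T2".
- **Primary analysis** (Statistical Analysis): a T1-adjusted linear regression to "estimate the difference in the mean changes between the intervention and control arms at T2", with multiple imputation.
- **T3 analysis** (Statistical Analysis): "The secondary outcomes at T2 and T3 will be analyzed based on the primary analysis and the 2 sensitivity analyses".
- **Secondary outcomes** (Study Outcomes): the only secondary outcome said to come from the online safety questionnaire is "confidence when communicating on the internet about suicide, as measured via the purpose-designed #chatsafe online safety questionnaire at T2". The safety or knowledge score at T3 is not listed.
- **Data collection** (Table 1): the row "Purpose designed #chatsafe online safety questionnaire" is ticked at T1, T2 and T3, and all participants complete the same questionnaires whatever their arm.
- **Design** (Study Design): a "pragmatic, parallel, superiority randomized controlled design", with "time 3 (T3)—4-week postintervention".

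**The concern.** Hypothesis 4 is the trial's only claim about durability. As worded, it asks whether the intervention group's score holds up between T2 and T3, and the control group plays no part. Both arms answer the same questionnaire three times. A stable or rising score in the intervention arm could therefore reflect practice with the items as well as retained learning, and only the control arm can tell these apart. The Pilot Data section gives the lack of a control group as the pilot's limitation and the reason for this trial, so a within-arm durability claim would bring that limitation back at T3.

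The analysis text does not close the gap. It says which outcomes receive a T3 analysis, and the score that hypothesis 4 needs is not among them. Followed literally, the plan either leaves that score without a T3 analysis or leaves the contrast to be chosen later.

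**Working it through.** **Step 1. Set the sections side by side.**

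| Element | Hypothesis 4 | T3 analysis as stated |
|---|---|---|
| Comparison | T2 against T3, intervention arm only | Intervention against control |
| Outcome | Knowledge of the guidelines (online safety questionnaire, by way of hypothesis 1) | Secondary outcomes; from this questionnaire, confidence only |
| Baseline adjustment | None implied | T1 score |
| Data at T3 | Collected, both arms | Collected, both arms |

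The two columns differ in both comparison and outcome. The data needed to reconcile them will exist. That the knowledge in hypothesis 4 means the online safety score is an inference from hypothesis 1, but no other listed measure fits.

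**Step 2. The plan's own figure.** Sample Size and Statistical Power gives about 400 participants (200 per arm), 5% significance and 80% power for the primary outcome, with no effect size or SD. The figure cannot be reproduced. Solving backwards (two-sided, normal approximation), the detectable difference is (1.960 + 0.842) × √(2/200) = 0.280 SD. It concerns T2 and says nothing about hypothesis 4.

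**Step 3. How informative a within-arm T2-T3 test would be (illustration only).**

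Inputs:
- The T2-T3 correlation ρ is assumed at 0.5 and 0.7.
- The gain is taken as 0.28 SD (step 2) and half of it is assumed lost, so the true loss is 0.14 SD.
- The upper n is 200, with nobody lost.
- The lower n is 75, from pilot completion: 189/507 = 37.3%, and 200 × 0.373 ≈ 75.

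Formulas:
- SE of within-arm change = √(2(1−ρ)/n).
- 95% CI half-width = 1.96 × SE.
- P(non-significant) = 1 − [Φ(0.14/SE − 1.96) + Φ(−0.14/SE − 1.96)].

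| n | ρ | SE | Half-width (SD) | P(non-significant) |
|---|---|---|---|---|
| 200 | 0.5 | 0.071 | 0.139 | 49% |
| 200 | 0.7 | 0.055 | 0.107 | 28% |
| 75 | 0.5 | 0.115 | 0.226 | 77% |
| 75 | 0.7 | 0.089 | 0.175 | 65% |

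On these assumptions, failing to detect a decline is weak evidence that there was none.

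**Step 4. Precision of the controlled alternative.** The change from T2 to T3 in the between-arm difference has variance 2 × 2(1−ρ)/n with n per arm, so its SE is √2 times the within-arm one. The half-widths become:
- n = 200: 0.139 × 1.414 = 0.196 SD (ρ = 0.5) and 0.107 × 1.414 = 0.152 SD (ρ = 0.7).
- n = 75: 0.226 × 1.414 = 0.320 SD and 0.175 × 1.414 = 0.248 SD.

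The controlled contrast answers the right question, but less precisely.

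**The case against.** The strongest reply is that the trial is controlled throughout. The Aims section opens by saying that the treatment group is compared with controls, and the stated T3 analysis is between arms, T1-adjusted and imputed. Study Outcomes labels secondary outcomes 1 to 3 as T2 measures, yet Statistical Analysis takes secondary outcomes to T3. The time labels are therefore not exclusive, and a sympathetic reader would assume that the online safety score is treated the same way at T3. Confidence, from the same questionnaire, clearly is. A margin for maintenance or a T2-T3 contrast could also sit in an analysis plan that is not shown.

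Much of this stands. The absence of a margin or a detailed contrast is not a finding, and T3 is not wholly unanalysed. It remains that the article does state which outcomes are analysed at T3, that the safety score is not among them, and that hypothesis 4 is phrased without the control arm. A reader has to assume the repair.

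A reader might also infer that a non-significant T2-T3 change will be reported as maintenance, or that an uncontrolled before-after test is planned. The document supports neither: it gives no T2-T3 test and no rule for judging hypothesis 4. These are risks left open by the wording.

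The figures in step 3 apply only if that risk materialised. They rest on assumed inputs and treat the analysis as complete-case, although imputation is planned. The case of 75 participants is pessimistic: the pilot intervention ran 12 weeks against 8 here, and this trial plans text-message reminders.

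**Conclusion.** The mismatch is real and can be checked from the text. Hypothesis 4 is a within-arm T2-to-T3 statement, while the stated T3 analysis is between arms and covers secondary outcomes that omit the online safety score. The T2 primary outcome and its analysis are untouched. What is at stake is whether the durability claim rests on the randomised comparison and on a contrast fixed in advance.

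The mismatch itself has no numerical size. The 28-49% (n = 200) and 65-77% (n = 75) chances of missing a 0.14 SD loss show why a within-arm reading would be weak, conditional on the assumed gain, loss and correlations. They do not describe a planned analysis.

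**What to change.** 1. List the #chatsafe online safety score at T3 as a secondary outcome in Study Outcomes.
2. Analyse it with the model already described for T2: between-arm linear regression adjusted for T1, with multiple imputation.
3. Restate hypothesis 4 as the between-arm difference in that score at T3, with its 95% CI.
4. Report the change in the between-arm difference from T2 to T3 descriptively, with a CI. Add that the absence of a significant decline will not by itself be described as maintenance.

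**Cost:** some rewording and one additional secondary analysis. The data are already collected in both arms. The change in the difference will be estimated less precisely than a within-arm change (step 4), so it should be described and not used as a test of maintenance.

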### Pilot Data

The #chatsafe intervention was tested in a pilot study in 2019-2020 [13]. The aims were to assess the acceptability, safety, and feasibility of the intervention as well as its impact on perceived self-efficacy, willingness to intervene against suicide on the internet, and safety of web-based communication about suicide. The study adopted a single-group pre- and posttest design. Participants were 189 young people aged 16-25 years recruited from 3 states in Australia via social media advertising. The intervention comprised 3 #chatsafe posts each week on the #chatsafe Instagram page. Participants were sent 1 post via direct message each week, for a period of 12 weeks. The results indicated that participants found the intervention acceptable. Participants also demonstrated improvements in perceived ability (*P*<.001) and intent to intervene against suicide (*P*<.001), and in several domains of internet self-efficacy, for example, problem-solving on the internet (*P*<.001). They also demonstrated improved web-based behavior, including monitoring their social media posts and responding directly to someone who may be suicidal.

Although these findings painted a promising picture, the pilot study was limited by the lack of control group. Therefore, the aim of this study is to test the efficacy of the #chatsafe intervention in a randomized controlled trial (RCT).

